#### Intervention group

2.3.1

First, the kindergarten educators of the intervention group will receive a planned 4-day (40 h) training of the Kneipp concept (see Figure 2: Curriculum Overview. Kneipp Educator Training) (10). The training will be focused on integrating the Kneipp concept with young children in the kindergarten setting with the 5 elements. Educators from intervention facilities will be trained together to allow an exchange among participants, enhance collective learning, share insights, and foster an environment for discussions. The training program will be conducted by two experienced trainers from Kneipp-Bund e.V.: one with expertise in hydrotherapy and mind–body practices, and the other specialized in herbs and nutrition.

**Figure 2 fig2:**
[figure not shown]
Curriculum overview. Kneipp Educator Training.

The waitlist group will also complete the training after the last data collection period. While there will be project mandate as to which interventions must be conducted, the educators in the intervention group will be encouraged to commence interventions directly after the training, particularly with emphasis and daily practice of cold-water applications. (see Figure 1: Five Elements of Kneipp) Intervention activities will be reported on a weekly basis by the kindergartens and recorded by the team. Furthermore, a qualitative methodology is employed to evaluate whether introducing the Kneipp concept will affect factors such as stress levels, quality of work in the kindergarten environment, interactions among children and educators. This involves conducting focused ethnography (15) on two separate days (one in spring/summer and one in autumn/winter) to obtain a better overview of the applications used in different seasons. Semi-structured interviews will be conducted with educators and kindergarten directors to understand and evaluate the use of the interventions, as well as to detect possible changes among kindergarten group dynamics and kindergarten educators. Maximum variation sampling strategy will be applied to provide rich and diverse perspectives, used for answering the qualitative research question. All kindergarten directors and at least 2 other educators from all the intervention facilities will be interviewed. The interviews will be conducted in the kindergarten facilities by a medical doctorate student (MG) until data saturation is reached. Throughout the process regular meetings with a group of qualitative researchers will be organized, where the means of data collection and analyzing process will be discussed, evaluated and reflected.

Another focus of the qualitative evaluation is to assess the feasibility of conducting larger multi-centric randomized studies in this context and the potential future implementation of hydrotherapy in kindergartens.

#### Waitlist group

2.3.2

The educators in the waitlist group serving as the control will not begin practicing the Kneipp concept until after the second data collection period, after which they will participate in a training.

### Outcomes

2.4

The primary outcome measure is the number of absent days due to illness among 2-6-year-old children in randomized Berlin kindergartens for the Kneipp concept intervention kindergartens compared to the matched waitlist kindergartens over two time points (baseline prior to the intervention and 12 months after baseline).

Additionally, the CCQ (16) and the NCI-CTCAE Scales (17) describing gastroenterological-based symptoms will be used as a secondary outcome measure at each of the two timepoints as well. The study will also gather data on the number of days educators are absent due to sickness. This information will be subjected to statistical analysis as an additional secondary outcome measure, aiming to identify potential correlations between the absence of educators and that of the children.

Summarized findings will identify categories and themes from the qualitative content analysis of observations and interviews highlighting the practice and experiences of implementing Kneipp in the kindergarten and perceived changes.

### Sample size

2.5

The sample size selection was formed by a preceding non-randomized controlled study (8) which focused on kindergarten sick days as a primary outcome. The study employed a Chi2-Test (categorizing kindergarten sick days as yes/no), revealing an effect size of *ω* (omega) = 0.41, equivalent to a Cohen’s *d* = 0.66 (8). Recognizing the non-randomized nature of the prior trial, the effect size was conservatively adjusted in half to φ (phi) = 0.205. With standard parameters set at *α* (alpha) = 0.05 (indicating a 5% probability of error in two-sided testing for differences), a power of 80% (*β* (beta) = 0.20), and accounting for an estimated dropout rate of approximately 20%, the optimal sample size for the current study was determined to be 240 child participants. The number of recruited matched kindergarten pairs will be based on the total calculated sample size.

Using a sampling strategy of maximum variation, semi-structured qualitative expert interviews will be planned with up to 15 kindergarten educators in the intervention facilities, while two focused ethnography observations will be each of the intervention kindergartens.

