## Methods

2

The Kita Kneipp Study is a confirmatory, mixed-method, two-armed, waitlist, clinical, cluster RCT that was registered with the German Clinical Trial Register (DRKS-ID: DRKS00029275) on November 10, 2022 (submission for registration June 22, 2022), and approved by the Ethics Committee of the Charité - Universitätsmedizin Berlin (Application number: EA2/122/22, approved on September 13, 2022). It follows the standards of the Helsinki convention of good clinical practices.

This study protocol follows the SPIRIT (Standard Protocol Items: Recommendations for Interventional Trials) Guidelines for reporting study protocols (11).

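### The 240-child sample size treats children as independent, so the stated 80% power is not supported for this matched-pair cluster-randomised trial

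*Protocol article*

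**What the plan says.** Section 2 (Methods) describes a "two-armed, waitlist, clinical, cluster RCT". Sections 2.3 and 2.6 say that kindergartens are matched in pairs on neighbourhood socio-demographic data and that one of each pair is randomised to immediate start and the other to the waitlist.

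Section 2.5 (Sample size) takes its effect size from an earlier non-randomised study: "The study employed a Chi2-Test (categorizing kindergarten sick days as yes/no), revealing an effect size of" omega = 0.41. Because that study was not randomised, "the effect size was conservatively adjusted in half to φ (phi) = 0.205". Alpha is 0.05, glossed as "indicating a 5% probability of error in two-sided testing for differences". Power is 80% and dropout about 20%. The conclusion is that "the optimal sample size for the current study was determined to be 240 child participants". The number of clusters then follows from the number of children: "The number of recruited matched kindergarten pairs will be based on the total calculated sample size".

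Section 2.5 names no ICC, cluster size, design effect or number of kindergartens. Section 2.8 analyses the sick-day count by negative binomial regression with group and baseline sick days as predictors, and uses kindergarten identifiers to see whether there is a cluster effect.

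**The concern.** The unit of randomisation is the kindergarten, but the calculation counts children as if each had been randomised separately. Children in one kindergarten share exposure to the same infections, and the Introduction itself points to cross-infection there as part of the burden of illness. Some positive ICC for illness absence is therefore to be expected, and any positive ICC reduces the information carried by a fixed number of children.

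The trial is presented as confirmatory. If it finds no difference, readers will judge that result against the stated 80% power. If the power was lower, a null result could be taken as adequately powered evidence against a benefit when it is not.

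**Working it through.** **Inputs from section 2.5:** w = phi = 0.205; two-sided alpha 0.05 (z = 1.960); power 80% (z = 0.842); dropout 20%; stated total 240.

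**1. Reproduce the stated figure, children independent.**

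n = (1.960 + 0.842)² / 0.205² = 186.8, so 187. The exact non-central chi-square also gives 187 (power 80.05%).

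Dropout: 187 / 0.8 = 233.75, so 234. The stated 240 is within 3% of this. The shortcut 187 × 1.2 gives 225, which fits less well.

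The chi-square inputs and dropout thus explain essentially the whole of 240.

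**2. What room is left for clustering?**

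Evaluable children out of 240: 240 × 0.8 = 192. Largest design effect (DE) that still gives 80% power: 192 / 186.8 = 1.028.

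With DE = 1 + (m − 1) × ICC, the largest tolerable ICC is 0.028 / (m − 1):
- m = 10: 0.028 / 9 = about 0.003
- m = 20: 0.028 / 19 = about 0.0015
- m = 30: 0.028 / 29 = about 0.001

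This step needs no assumed ICC and no number of kindergartens.

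**3. Illustration of the loss.** The article gives neither the ICC nor the number of kindergartens K, so both are assumptions here: ICC 0.01 to 0.10, and K = 10 or 14. There are 187 evaluable children, so m = 187/K = 18.7 or 13.4. Effective n = 187/DE. Large-sample power uses a 1-df chi-square with non-centrality effective n × 0.205². The t columns use a non-central t with non-centrality 0.205 × √(effective n). One has K − 2 df (unmatched). The other has K/2 − 1 df (paired), with no reduction in variance credited to the matching.

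| K | ICC | DE | Effective n | Power, large-sample | Power, t with K − 2 df | Power, t with K/2 − 1 df |
|---|---|---|---|---|---|---|
| 10 | 0.01 | 1.18 | 159 | 73% | 62% | 50% |
| 10 | 0.02 | 1.35 | 138 | 67% | 56% | 45% |
| 10 | 0.05 | 1.89 | 99 | 53% | 44% | 35% |
| 10 | 0.10 | 2.77 | 68 | 39% | 32% | 25% |
| 14 | 0.01 | 1.12 | 166 | 75% | 68% | 60% |
| 14 | 0.02 | 1.25 | 150 | 71% | 64% | 56% |
| 14 | 0.05 | 1.62 | 116 | 60% | 53% | 46% |
| 14 | 0.10 | 2.24 | 84 | 47% | 41% | 35% |

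Worked row (K = 10, ICC 0.05): DE = 1 + 17.7 × 0.05 = 1.885; 187 / 1.885 = 99.2; non-centrality 99.2 × 0.042025 = 4.17; power 53%.

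All figures are for the unadjusted yes/no comparison on which 2.5 is based.

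**The case against.** **The condensed format.** An article may leave detail to a full protocol, so a design effect might sit there. This fails: step 2 shows that the published inputs already use up 240, so no meaningful allowance can be hidden in it. Section 2.5 also gives a complete calculation with a power attached.

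**The planned analysis differs from the one used for sizing.** The regression in 2.8 uses the full count and adjusts for baseline sick days, and the pairs are matched. Each may recover precision. This stands as a limit on the size of the loss. It does not rescue the 80%, because 2.5 claims no such gain.

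**The number of kindergartens.** A reader might infer 5 to 7 intervention kindergartens from the interview plan: up to 15 interviews in 2.5, and in 2.3.1 "All kindergarten directors and at least 2 other educators from all the intervention facilities will be interviewed". That gives 15/3 = 5 facilities, or 15/2 = 7 if only the two educators are counted. But it divides a ceiling by a minimum, so at best it bounds the number from above. Section 2.3.1 also ties the interviews to data saturation. K = 10 and 14 are therefore assumptions. Fewer kindergartens would make power worse.

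**A floor on the p-value.** A reader might note that with 5 pairs a within-pair randomisation test cannot go below 2/2⁵ = 0.0625, and conclude that at least 6 pairs are required. The arithmetic is right, but 2.8 plans a model-based test and the article states no number of pairs, so this cannot be held against the plan.

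**Conclusion.** The point holds. The stated 80% power belongs to a trial that randomises 240 children individually. For this trial it is unsupported, and it is too high for any appreciable within-kindergarten correlation: the margin is a design effect of about 1.03. That conclusion rests only on the figures in 2.5 and on the fact that kindergartens are randomised.

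The size of the shortfall is illustrative. Under the assumed 10 to 14 kindergartens, large-sample power is about 73–75% at ICC 0.01, 67–71% at 0.02, 53–60% at 0.05 and 39–47% at 0.10. It is lower with a t reference for few clusters.

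A reader might go further and say that true power is known to be far below 80%. The article does not support that. It gives no ICC, at ICC 0.01 the large-sample loss is modest, and any gain from matching and baseline adjustment is unquantified. Nor is this an arithmetic slip: the calculation reproduces, but it is the calculation for a different design.

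**What to change.** In section 2.5:

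1. Remove the claim that 240 children give 80% power.
2. State the number of kindergarten pairs, the mean number of consenting children per kindergarten and an assumed ICC range, labelled as an assumption.
3. Apply DE = 1 + (m − 1) × ICC, with a small-sample reference distribution that matches the planned analysis.
4. Report the resulting power and detectable effect for 240 children across that range, and state any gain assumed from matching or from adjustment for baseline sick days.

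The cost is a rewording of one section and a less favourable stated power. No extra children are needed. Recruiting more kindergartens is not part of this fix: it would not be a cheap change, and with measurement planned for autumn 2022 and autumn 2023 it may come too late. The corrected statement is useful even after recruitment has closed, because it is needed to interpret a null result.

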### Recruitment, randomization, and assignment of intervention

2.6

Gate keepers at the Berlin governing structures responsible for kindergartens, contact leads from cooperative partners in Berlin will identify interested kindergartens. Members of the study team (SB – experienced scientific researcher, study coordination, AT – study administration) will contact these via email in which a flyer about the project will be included as additional information. Once interested, kindergartens will be contacted via telephone and site feasibility will be assessed for inclusion.

After being recruited to the study, kindergartens with a similar socio-economic level will be match-paired according to statistical demographic analysis of locations in Berlin (14).

The kindergartens will then be randomized within their matched pair to either the intervention or the waitlist group using the randomizing function of Python 3.10.6, executed by an experienced biostatistician (FK). The allocated study group will not be blinded, as this would not be possible due to the nature of the interventions. Therefore, the kindergartens, caregivers and children will be aware whether they are in the Kneipp or in the waitlist group.

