### Statistical methods

2.8

The study will be published in a peer-reviewed academic journal. Analyses of data will be performed after the collection is finalized according to the following hypotheses:

Primary Efficacy Hypothesis (Infection days leading to absence):Primary Null Hypothesis (H0): Implementation of a child-friendly Kneipp concept in the kindergartens does not lead to a significant reduction in infection-related absenteeism, after 12 months.Alternative Hypothesis (H1): Implementation of child-friendly Kneipp concept in the kindergartens results in a significant reduction in infection-related absenteeism, after 12 months.

Participant characteristics, stratified by groups (Kneipp vs. Control) will be presented. For continuous variables, descriptive statistics such as mean, standard deviation, and range will be calculated, while frequencies and percentages will be used for categorical variables.

The primary outcome will be the number of sick days reported to the kindergarten. To account for the expected overdispersion (right-skewed data because of high zero counts) in the count data, we will employ a negative binomial regression model. This model will include the group (Kneipp vs. Control) and the number of sick days at baseline as predictors. We will integrate unique kindergarten identifiers to determine if cluster effects exist.

For secondary outcome analysis, we will conduct an independent t-tests to compare the mean Common Cold Questionnaire (CCQ) scores between the Kneipp and Control groups. To investigate the interaction effects of group and sex, and group and age on CCQ scores, a two-way ANOVA will be performed. This model will include the main effects of group, sex, and age, as well as their interactions. If significant interactions are identified, post-hoc analyses will be conducted. Correlation analysis will involve calculating Spearman’s correlation coefficients to assess the relationships between CCQ scores and the number of sick days, and between CCQ scores and age. The correlation (ρ) will be interpreted based on conventional guidelines. To compare the frequencies of health outcomes such as colds, bronchitis, lung inflammation, antibiotic use, and gastrointestinal infections between the Kneipp and Control groups, chi-square tests will be performed. If the assumptions of the chi-square test are violated due to expected frequencies being less than 5, Fisher’s exact test will be used instead.

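### The 80% power in section 2.5 is computed for independent children and leaves the number of pairs to follow from 240; with few pairs, cluster-respecting inference falls well short of 80%

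*Protocol article*

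**What the plan says.** The protocol article describes the trial as confirmatory and cluster randomised (section 2: "The Kita Kneipp Study is a confirmatory, mixed-method, two-armed, waitlist, clinical, cluster RCT"). Section 2.6 sets the unit of randomisation: "The kindergartens will then be randomized within their matched pair to either the intervention or the waitlist group".

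Section 2.5 computes the sample size from a chi-square test on sick days coded yes/no. The effect comes from a preceding non-randomised study: "the effect size was conservatively adjusted in half to φ (phi) = 0.205". Alpha is 0.05, "indicating a 5% probability of error in two-sided testing for differences", power is 80% and dropout is about 20%. The result is that "the optimal sample size for the current study was determined to be 240 child participants". The number of pairs is then tied to that total: "The number of recruited matched kindergarten pairs will be based on the total calculated sample size". The section gives no number or minimum of pairs, no kindergarten size, no ICC and no design effect.

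Section 2.8 fixes the primary analysis: "we will employ a negative binomial regression model", with group and baseline sick days as predictors. Kindergarten identifiers are added to see whether cluster effects exist. The pair is not mentioned, and no randomisation test is planned.

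**The concern.** Chance is applied to kindergartens within pairs, so the number of pairs governs how much the randomisation can show. Section 2.5 works the other way round: the child total is fixed and the pairs follow from it. A few large kindergartens can therefore meet the target. The stated 80% then describes a trial of independently randomised children, not the one designed.

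Two things are at stake. The first is power: inference that respects the clusters has few degrees of freedom, and any correlation within kindergartens lowers the power further. The second is the basis of a positive result: with very few pairs, a significant regression coefficient has little support from the randomisation and depends on the model handling the clusters correctly. Raising the child total alone would not settle either point, because a larger total can again come from a few large kindergartens.

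**Working it through.** **Inputs from section 2.5:** phi = 0.205, two-sided alpha 0.05, power 80%, dropout about 20%, total 240. **Assumptions, because the article gives no figure:** equal enrolment per kindergarten; ICC of 0 and 0.05 in the main table, with 0.01 to 0.10 as the wider range; no gain from matching or from the baseline covariate.

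**1. Reproducing 240.** N = (1.960 + 0.842)² / 0.205² = 187 evaluable children. Dropout: 187/0.8 = 234, within 3% of 240. The calculation contains no allowance for clustering. In reverse, 240 × 0.8 = 192 evaluable children give a noncentrality of √192 × 0.205 = 2.84 and normal-theory power of 81%.

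**2. Pairs that satisfy 240.** Pairs k = 240/(2 × children enrolled per kindergarten). The article gives one indirect sign of k. Section 2.3.1 requires interviews with every director and at least two other educators in each intervention facility, at least three per facility, while section 2.5 caps the interviews at 15. That implies at most 15/3 = 5 intervention kindergartens if directors count toward the 15, and at most 7 if they do not (15/2, rounded down).

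**3. Power with cluster-level inference.** The design effect is DE = 1 + (n − 1) × ICC, with n = 192/(2k) evaluable children per kindergarten. The noncentrality is √(192/DE) × 0.205. Power is taken from the noncentral t with k − 1 df (pair-level) or 2k − 2 df (unpaired, kindergarten-level).

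| Enrolled per kindergarten | Pairs k | ICC 0: pair-level / unpaired | DE at ICC 0.05 | ICC 0.05: pair-level / unpaired |
|---|---|---|---|---|
| 10 | 12 | 73% / 77% | 1.35 | 61% / 65% |
| 20 | 6 | 63% / 73% | 1.75 | 41% / 49% |
| 24 | 5 | 57% / 70% | 1.91 | 35% / 44% |
| 30 | 4 | 49% / 66% | 2.15 | 27% / 37% |
| 40 | 3 | 36% / 57% | 2.55 | 19% / 28% |

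Example for five pairs at ICC 0.05: n = 19.2, DE = 1 + 18.2 × 0.05 = 1.91, noncentrality = √(192/1.91) × 0.205 = 2.06, and the critical values are 2.776 (4 df) and 2.306 (8 df).

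Even before any loss for degrees of freedom, five pairs give about 74%, 68%, 54% and 39% at ICC 0.01, 0.02, 0.05 and 0.10.

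**4. Exact within-pair randomisation test.** There are 2^k equally likely allocations, so the smallest two-sided p is 2/2^k: 0.25, 0.125, 0.0625 and 0.031 for 3, 4, 5 and 6 pairs. Six is the first number that can fall below 0.05, and then only if all six differences have the same sign. With noncentrality 2.84 at ICC = 0 and normal pair differences, that has probability of about Φ(2.84/√6)⁶ = 0.877⁶ = 45%.

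**5. What a model-based p-value rests on.** A null simulation used 5 pairs, 19 children per kindergarten, an assumed mean of 3 days and dispersion of 1, with no baseline covariate. Child-level negative binomial regression ignoring clusters gave p < 0.05 in about 5% of trials with no between-kindergarten variation. This rose to 14%, 20% and 31% at between-kindergarten SDs of 0.2, 0.3 and 0.4 on the log scale. A paired t test on the pair differences stayed at 4% to 6%.

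**The case against.** The strongest objection concerns a reading that the floor of 0.0625 invites: that with five or fewer pairs the trial cannot be significant at two-sided 5%, and so cannot support a confirmatory claim. The protocol does not support that. The floor belongs to an exact randomisation test, which section 2.8 does not plan. The planned negative binomial regression has no such floor, and a paired t test on five differences rejects at |t| > 2.776. The 57% power above for five pairs itself shows that significance is attainable.

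Other points stand in part:

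- The pair-level test is not the planned one, and section 2.8 has no pair term. This is why the unpaired figures are shown beside it; they are higher but remain below 80%.
- If the ICC were exactly zero, a child-level analysis would be valid and would keep about 81%. That is correct. The ICC = 0 columns show the price of inference that allows for clusters, and ten or fewer clusters cannot establish that the ICC is zero.
- Good matching, baseline adjustment and a count outcome in place of yes/no could each recover some power. The article gives no figure for any of them.
- Kindergarten size is assumed, and the wording only bases the pairs on the total. The full protocol may name a number of pairs. The 80% is nevertheless stated here, for a calculation that ignores the clusters.
- A full cluster calculation with ICC and kindergarten size would itself return a number of clusters, so this point overlaps with the missing design effect. The degrees of freedom still have to be part of that calculation.

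**Conclusion.** The concern holds for the stated power. Section 2.5 gives 80% for 240 independent children and sets no lower limit on the pairs that may supply them. Across 12 to 3 pairs, no cluster-level calculation reaches 80%. For 6 to 3 pairs at ICC = 0, power falls from 63% to 36% (pair-level) or from 73% to 57% (unpaired), and at ICC 0.05 it is 41% to 19% or 49% to 28%. The article's interview figures make five to seven pairs or fewer plausible but do not fix the number. These results assume the kindergarten sizes and ICC shown, equal clusters, and the protocol's own phi and dropout.

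With five or fewer pairs, significance is possible but depends on the model and cannot be confirmed by an exact randomisation test. It does not follow that a confirmatory claim is out of reach.

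**What to change.** In section 2.5, replace the 80% figure with the power for the actual number of matched pairs. Use the cluster-level degrees of freedom of the analysis that will be run, and give the assumed kindergarten size and an ICC range. If there are five or fewer pairs, add that a significant result depends on the regression model with at most 10 clusters and cannot be confirmed by an exact within-pair randomisation test. This costs wording and a short recalculation only.

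If pairs are still being recruited, prefer spreading the same 240 children over more kindergartens, for example about 20 each at six pairs. Six is only the minimum for the exact test and does not give 80% power. This option is not free: each added intervention kindergarten needs suitable premises, two observation days and at least three interviews. At six intervention kindergartens that makes at least 18 interviews, above the planned maximum of 15 if directors count toward it, so the interview figure would have to be revised as well.
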